### Participant recruitment

Women who are completing prenatal visits associated with the parent study (at the second prenatal care visit occurring between 24 and 30 weeks) are provided information about the study by a member of the parent study staff. Participants who express interest in the infant follow-up study are encouraged to text the infant study coordinator at that time, and are provided the contact information. The infant study coordinator also are directly provided the list of names and contact information for all women who complete the second prenatal study visit and who consented to share this information. Continuing contact efforts consist of texts and phone calls, and women who express an interest in participating in the infant study are scheduled for enrollment approximately one week following their estimated date of delivery.

Women in the parent and infant studies move frequently and change phone numbers frequently. Efforts to reconnect include calling any listed contacts, and checks of White Pages. Ongoing efforts are made to enroll women in the study at any one of the study time points that they are contactable, unless or until participation is refused. Recruitment is ongoing and includes 185 study participants to date. Active refusals constitute 9%. Retention rates are approximately 80–85% throughout the infants’ first year.

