### Data collection

Maternal prenatal stress data are collected two times during pregnancy (at the first prenatal care visit occurring between 8 and 14 and at a later prenatal care visit occurring between 24 and 30 weeks). Prenatal stress measures include self-reported stressful life events, perceived stress, perceived discrimination, state anxiety and depressive symptoms, as well as hair cortisol collection. Medical record abstraction is conducted by trained research staff for evidence of pregnancy infections, complications and treatments, and laboratory outcomes. Post-delivery medical record abstraction is detailed for birth outcome (gestational age, birth weight, size-for-age), delivery type, and complications.

Postnatal study visits occur at five times (1-week, and 3-, 6-, 12-and 18-months) post-birth and consist of biological samples, questionnaire data, and infant assessments. Data collection is conducted in participants’ homes or at the university laboratory by experienced research staff, trained in all aspects of the protocol. To the greatest degree possible, all home visits except the 1-week visit are scheduled for ±2 weeks of the designated time; the 1-week visit are scheduled for ±2 days. For infants born premature, the initial 1-week visit (and other follow up visits) are scheduled according to the corrected gestational age.

Enrollment and consent occur at the first postpartum study visit in which the dyad participates. Mothers provided consent for their own and their infant’s participation. Following consent, infant neurodevelopmental assessments (*NICU Network Neurobehavioral Scale* [NNNS] at 1-week [41] or Bayley Scales at 3-,6-,12-, and 18-month visits [42]) and growth measures (height, weight, and head circumference) are administered by trained research staff while the mother fills out questionnaires concerning her current demographic status, her home environment, her recent stress, her infant’s diet, and her and her infant’s sleep and health. At the 3-, 6-, 12- and 18- month visits, mothers and infants are then videotaped during a 5 min structured and a 5 min unstructured mother child interaction. At the one week and 18-month visits, blood is collected from the infant via heel stick and finger stick respectively, for the purpose of assessing cytokine levels (PNI functioning). Swabs are then used to collect infant cheek cells for DNA analyses at the 3-month visit.

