### Power calculations

The study will enroll approximately 300 mother-infant dyads from the parent study for further follow-up. Because of the various complex relationships hypothesized in this project, power calculations were carried out using Monte Carlo simulations of hypothesized data generating processes permitting empirical estimation of coverage and power as a function of sample size and standardized effect sizes, *d:*
$$ \frac{\left({\mu}_1-{\mu}_0\right)}{\sigma } $$. Aim 1 concerns the association between prenatal stress (measured in the parent study) and infant microbiome at baseline for the follow-up study, thus the full sample will be available. Using multiple indicator variables for the latent construct of prenatal stress can reduce measurement error and improve power. For example we estimate 93% power to detect a correlation between prenatal stress and Shannon Index of diversity of *r = .22*, and 78% power to detect a correlation of *r = .18*. Aims 2 and 3 rely on analysis of repeated measures data at 1 week, 3-, 6-, 12-and 18-months; based on investigator experiences in longitudinal studies we anticipate at most 20% loss to follow-up resulting in N = 240 for longitudinal analyses. For example for Aim 3 we estimate 82% power to detect correlation in microbiome diversity and the rate of change (latent slope) in the Bayley of *r = 0.15*. Power is similar for other longitudinal hypotheses.

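### The 82% power stated for Aim 3 does not follow from its printed inputs: r = 0.15 in 240 infants gives about 64% at two-sided 5%, even with error-free slopes

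*Protocol article*

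**What the plan says.** All the figures are in the Power calculations section of the protocol article. Enrolment is about 300 dyads, and the full sample is taken to be available for Aim 1. For that aim the section gives 93% power at r = .22 and "78% power to detect a correlation of" r = .18. For Aims 2 and 3, "we anticipate at most 20% loss to follow-up resulting in N = 240 for longitudinal analyses". For Aim 3, "we estimate 82% power to detect correlation in microbiome diversity and the rate of change (latent slope) in the Bayley", with the correlation set at 0.15. The paragraph closes: "Power is similar for other longitudinal hypotheses".

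The section says that power came from Monte Carlo simulation. It gives no alpha, no sidedness, and no variances or reliabilities. The Statistical plan mentions a Bonferroni correction where appropriate, which could only lower power.

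**The concern.** The correlation between a predictor and a latent slope is a between-infant quantity. More Bayley visits make each infant's slope more precise, but they add no infants. With no covariate adjustment, the best the design can do is the power of a simple correlation in 240 pairs with every slope known exactly. The printed 82% lies well above that.

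The paragraph also looks inconsistent within itself. Aim 3 has a smaller correlation and fewer infants than the second Aim 1 example, yet is given the higher power.

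Aim 3 is the link from microbiome to neurodevelopment. A reader of a null result would take it that a true r = 0.15 had an 18% chance of being missed. On the printed inputs at two-sided 5% that chance is at least 36%.

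**Working it through.** **Inputs.** From Power calculations: r = 0.15, N = 240 (300 × 0.80), stated power 82%; for Aim 1, r = .18 and .22, N about 300, stated power 78% and 93%. Alpha is not stated; two-sided 5% is assumed and one-sided values are also shown.

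**Formula.** Fisher z: power = Φ(atanh(r) × √(N − 3) − z), where z = 1.960 (two-sided 5%) or 1.645 (one-sided 5%).

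**1. Trying to reproduce 82%.** atanh(0.15) = 0.1511 and √237 = 15.39, so the noncentrality is 2.33.
- Two-sided 5%: Φ(2.33 − 1.96) = 64.3%
- One-sided 5%: Φ(2.33 − 1.645) = 75.2%
- One-sided 10%: 85.2%
- N = 300, two-sided 5%: 74.1%
- N = 300, one-sided 5%: 83.1%

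Only the last is close to 82%. It needs a one-sided test, no dropout and error-free slopes, and it falls to 75% at slope reliability 0.8. At N = 240, reaching 82% would take an alpha of about 0.16 two-sided (0.08 one-sided).

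**2. Cross-checks at two-sided 5%, error-free slopes.** The noncentral t for a regression slope gives 64.8%. A simulated growth model with four Bayley visits (8,000 replicates) gives 64.4%.

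**3. Slope error.** With reliability ρ the observable correlation is 0.15 × √ρ. The documents give no ρ, so these values are assumptions:

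| Assumed ρ | Fisher z | Simulation |
|---|---|---|
| 1.0 | 64% | 64% |
| 0.8 | 55% | 55% |
| 0.6 | 44% | 44% |
| 0.4 | 31% | 30% |

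**4. What 82% would require** (two-sided 5%, error-free slopes).
- Infants: ((0.915 + 1.960) / 0.1511)² + 3 ≈ 365
- Correlation at N = 240: tanh((0.915 + 1.960) / 15.39) ≈ 0.185
- For comparison, r = 0.18 at N = 240: Φ(0.1820 × 15.39 − 1.96) ≈ 80%

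**5. Aim 1 beside Aim 3.** For r = .18 and N = 300 the error-free noncentrality is 0.1820 × √297 = 3.14, against 2.33 for Aim 3. At two-sided 5%, error-free power for Aim 1 is 88.0% (r = .18) and 97.1% (r = .22). The stated 78% and 93% lie below those bounds, as measurement error would make them; reliabilities of about 0.76 and 0.80 would account for them. The Aim 3 figure lies about 18 points above its own bound (82 − 64). Attenuation like that in Aim 1 would put Aim 3 at about 53–55%.

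**The case against.** The strongest defence is that the figure came from simulation and that Fisher z assumes no covariates. Analysis for Aim 3 does plan growth models with time-varying and time-invariant covariates. If covariates unrelated to diversity explained a share R² of slope variance, the effective correlation would rise to about 0.15 / √(1 − R²). Reaching 82% at N = 240 would need R² of about 1 − (0.15/0.185)² = 34% two-sided, or about 17% one-sided. This part stands: a reader might conclude that 82% is impossible, or that 64% is an absolute ceiling, and the documents do not support that. Both statements depend on alpha and on no covariate gain. But the text gives neither a covariate gain nor a lenient alpha as an assumption of the calculation. The comparison with Aim 1 likewise presumes a common alpha, which is not stated.

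Three other stronger readings should not be drawn.
- A reader might infer that the study would more likely than not miss r = 0.15. At two-sided 5% that requires slope reliability below about 0.71. The documents give none, and at 0.8 power is still 55%.
- A reader might see a conflict between five waves in the power paragraph and "Bayley Scales at 3-,6-,12-, and 18-month visits". The five waves describe the repeated-measures data for Aims 2 and 3 together. Stool is collected at all five visits and the NNNS is given at 1 week, so there is no contradiction.
- A reader might think 240 too optimistic, because Participant recruitment says "Retention rates are approximately 80–85% throughout" the first year while follow-up runs to 18 months. Those rates are compatible with at most 20% loss. Even if first-year loss continued at a constant rate (assumed), N would be 300 × 0.80^1.5 ≈ 215 to 300 × 0.85^1.5 ≈ 235, and power 60–63%.

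It is also fair to say that the Aim 3 figure is offered as an example in a cohort already enrolling. That bears on how much must change, not on whether the figure is right.

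**Conclusion.** Wrong as written. On the printed r and N, power for Aim 3 is about 64% at two-sided 5%, or 75% at one-sided 5%, with error-free slopes and no covariate adjustment. The stated 82% exceeds these by about 18 and 7 points. Slope error widens the gap by an amount the documents do not let one fix. The ordering against Aim 1 points the same way if both aims use one alpha. The supportable statement is that 82% cannot be reproduced from the stated inputs.

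The closing sentence on other longitudinal hypotheses refers back to this figure and so needs checking. No r, N or power is printed for Aim 2, so no specific error there is shown.

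**What to change.** Re-run the Aim 3 simulation and state alpha, sidedness, the assumed slope reliability (preferably a range) and any share of slope variance attributed to covariates. Replace the 82% with the result. If no covariate gain is claimed, the best cases for N = 240 at two-sided 5% are about 64% for r = 0.15 and about 80% for r = 0.18. If a covariate gain is claimed, give its size and basis. Then recheck the sentence on the other longitudinal hypotheses and restate it to match.

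The cost is one simulation and a rewritten paragraph. No participants or procedures are added. The downside is a less favourable stated power for Aim 3.

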### Statistical plan

Our initial data analyses will include: 1) determining the distributions of outcome measures and assessing whether data transformations are needed, 2) insuring that the underlying assumptions of statistical analyses are satisfied, 3) identifying potential co-linearity problems, 4) identifying potential outliers that require further investigation, 5) confirmatory psychometrics for established psychosocial and developmental measures. For categorical variables, we will check for sparse cells and regroup categories if necessary. In building multivariable models, we will check linearity assumptions for continuous predictors and consider higher-order terms as appropriate. For missing data, sensitivity analysis will be performed to evaluate the impact of missing data on results, with consideration for implementing multiple imputation of missing values. We will apply Bonferroni correction when appropriate to adjust for multiple comparisons. Analyses will be carried out using R (including OpenMX SEM, and lme4 mixed modeling packages) and SAS.

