To best capture the richness of the data, analyses considering maternal prenatal stress will be carried out in a structural equation modeling (SEM) framework reducing measurement error for the latent construct of maternal prenatal stress. Based on exploratory examination of the measures we may consider a single latent prenatal stress variable, or possibly two (e.g. chronic/life course stress and acute anxiety/perceived stress). We will then estimate the association between the latent variable(s) and outcomes. Postnatal maternal stress measures will also be combined in a similar manner to capture overall stress burden across infant developmental periods. PNI function will be evaluated as the absolute levels of each cytokine and as the ratios of pro- to anti-inflammatory factors (e.g.*,* IL1/IL10), and may be log-transformed if indicated. Diurnal cortisol from the three samples will be estimated as the area under the curve (AUC). The NNNS total score will be incorporated into our analysis framework as our primary measure of newborn neurobehavior function. The Bayley III standardized scores for the mental, motor and behavioral instruments will be considered independently to separately characterize neurocognitive and socio-emotional development. Repeated administrations of the Bayley-III also allow for the analysis of trajectories of growth over time from 3- to 18-months of age.

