Preliminary testing will begin with a series of cross-sectional multivariable regression analyses testing the association between microbiome (e.g. Shannon Diversity Index) and PNI operationalized as the ratio of pro- to anti-inflammatory cytokines, or the cortisol AUC at each wave of follow-up. Next linear growth curve models with time invariant covariates and baseline microbiome predicting PNI trajectories will be fit to estimate the role of initial gut microbiome conditions on subsequent infant PNI trajectories. Finally fully longitudinal growth curve models including time-varying (e.g. microbiome measure trajectories) and time-invariant predictors will be estimated. Alternative mixed effects longitudinal models will be compared using Akaike Information Criterion (AIC) fit statistics. We will also test the association between PNI (now serving as a predictor variable) and infant development measured with the NNNS, and Bayley.

### Analysis for Aim 3

We will directly test the association between microbiome abundance or diversity, and trajectories in infant neurocognitive and socio-emotional development as measured using the Bayley. The modeling strategy will be similar to Aim 2 with initial exploratory and descriptive modeling followed by fitting a series of longitudinal growth curve models with time-varying and invariant covariates. Finally, we will include a series of candidate modifiers of the effect of microbiome on child development, operationalized as interaction terms. The candidate moderators include maternal post-natal stress, and maternal-infant interaction. These moderator models permit the estimation of possible heterogeneity of the association of microbiome and development.

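### The claim of similar power for other longitudinal hypotheses is unsupported for the Aim 3 moderator tests and for Bonferroni-adjusted tests, and the 82% it rests on does not reproduce as a simple correlation

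*Protocol article*

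**What the plan says.** The Power calculations section gives one longitudinal figure. From about 300 dyads, "we anticipate at most 20% loss to follow-up resulting in N = 240 for longitudinal analyses". On that basis it reports 82% power for a correlation of 0.15 between microbiome diversity and the latent slope of the Bayley. It then generalizes: "Power is similar for other longitudinal hypotheses". For those other hypotheses it names no effect size, alpha, sidedness or number of tests. The figures are attributed to Monte Carlo simulation, and the article does not show the settings.

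Three statements elsewhere in the Statistical plan show what the other hypotheses include:

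- Analysis for Aim 3 enters modifiers of the microbiome effect as interaction terms: "The candidate moderators include maternal post-natal stress, and maternal-infant interaction".
- On outcomes: "The Bayley III standardized scores for the mental, motor and behavioral instruments will be considered independently".
- On multiplicity: "We will apply Bonferroni correction when appropriate to adjust for multiple comparisons". The family of tests is not defined.

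**The concern.** The generalizing sentence is a positive statement about the design, not a detail left for another document. It extends the power of one main effect, on one microbiome measure, to tests of a different kind. A difference in association between subgroups is estimated less precisely than the association itself, and a Bonferroni-adjusted alpha lowers power for any effect of fixed size. The power section mentions neither.

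Moderation by postnatal stress and by mother-infant interaction is a named part of the Aim 3 analysis. If those interactions come out non-significant, a reader who relies on this sentence would take the result as coming from a study with roughly 82% power, and could wrongly conclude that caregiving and stress do not modify the association.

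**Working it through.** **Inputs from the article (Power calculations).** Enrolment 300, loss 20%, so 300 × 0.8 = 240, which agrees with the text. Aim 3 example: r = 0.15, stated power 82%.

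**Assumed, because not stated.** Two-sided alpha of 0.05 (one-sided also tried), the size and form of the interaction, and the number of tests in a Bonferroni family.

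**1. The plan's own figure.** Power ≈ Φ(atanh(r) × √(N − 3) − z), with atanh(0.15) = 0.1511 and √237 = 15.39, so the noncentrality is 2.327.
- Two-sided: Φ(2.327 − 1.960) = 64% (noncentral t: 65%).
- One-sided: Φ(2.327 − 1.645) = 75%.
- These treat the slope as perfectly measured. In simulation, slope reliability of 0.8 gives about 55% and 0.5 about 38% (two-sided).
- Two-sided 82% needs a noncentrality of 1.960 + 0.915 = 2.875. That means r = tanh(2.875 / 15.39) ≈ 0.185 at N = 240, or N = (2.875 / 0.1511)² + 3 ≈ 365 at r = 0.15.

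Because 82% does not reproduce this way, the steps below are given on both bases: direct (noncentrality 2.327) and the stated 82% at face value (2.875).

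**2. Interaction, two equal groups (assumed).** r = 0.15 in 120 infants and 0 in the other 120.
- SE of the difference in Fisher z = √(1/117 + 1/117) = 0.1307.
- 0.1511 / 0.1307 = 1.156, and Φ(1.156 − 1.960) = 21%.
- On the 82% basis, a slope difference equal to the main slope halves the noncentrality: 2.875 × 0.5 = 1.438, and Φ(1.438 − 1.960) = 30%.
- For 80% power: 2.802 × 0.1307 = 0.366 on the z scale, and tanh(0.366) ≈ 0.35 versus 0.

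**3. Interaction, continuous moderator (assumed).** Simulated regression at N = 240, two-sided 5%.
- Standardized interaction of 0.15: 64%, the same as the main effect in step 1.
- Half that size (0.075): 21%, or 30% on the 82% basis.
- 80% power needs a standardized interaction of about 0.18, since tanh(2.802 / 15.39) ≈ 0.18.

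**4. Bonferroni across the three Bayley scores only.** alpha = 0.05 / 3, critical z = 2.394.
- From the stated 82%: Φ(2.875 − 2.394) ≈ 68%.
- Direct: Φ(2.327 − 2.394) ≈ 47%.

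**5. Range across the scenarios tried.** At the low end, a half-size interaction with six tests (assumed: 3 scores × 2 named moderators) on the direct basis gives 7%. At the high end, an interaction as large as the main effect, unadjusted and on the 82% basis, gives 82%.

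**The case against.** The strongest reply is that the article's power came from simulating specified data-generating processes, and a simple-correlation formula is not that model. The formula also misses the Aim 1 figures: at N = 300 it gives 97% and 88%, where the article states "93% power to detect a correlation between prenatal stress and Shannon Index of diversity of *r = .22*, and 78% power" for r = .18. The settings may sit in a fuller protocol, which a condensed article need not repeat. This stands in part: the formula cannot prove the 82% wrong. The directions differ, however. The Aim 1 figures fall below the formula, as measurement error would produce. The Aim 3 figure lies above it, and an imperfectly measured slope would move power the other way. Some other feature, such as repeated microbiome measures, could explain it, but none is described.

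Second, the interaction sizes are mine. With a continuous moderator and an equally large standardized interaction, the sentence is right. A reader might infer that the sentence is simply false; step 3 of the working shows that it is not. What remains is that it depends on an unstated and demanding condition: with two equal groups, equal power needs roughly 0.30 versus 0, or +0.15 versus −0.15.

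Third, the Bonferroni rule is conditional and its family undefined, so a reader who infers that the power section breached the plan's own rule goes too far. The text supports only that no adjusted alpha is stated.

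Fourth, the moderators are called candidates and come last in the Aim 3 sequence. That wording is already tentative, which limits the importance of the point, but it does not exempt them from a sentence that covers all other longitudinal hypotheses.

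**Conclusion.** The point holds as an unsupported statement, not as a demonstrated error. Similar power follows for the moderator tests only if the standardized interaction is as large as the main effect and alpha is unadjusted. Departing from either condition lowers power materially: to 21% (30% on the 82% basis) for the two-group scenario, and to about 68% for a main effect adjusted for three Bayley scores.

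These are scenarios, not estimates. A reader might be tempted to say that real power for the moderator tests is some particular band, such as 20% to 50%. The documents give no interaction size, moderator split or test count from which to derive one, and the scenarios tried run from 7% to 82%. Nor does the sentence reach Aim 1, which is a baseline analysis on the full sample.

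The 82% benchmark is unexplained. It should be justified or corrected before it is extended to anything else.

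**What to change.** In Power calculations:

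1. Limit the generalizing sentence to main-effect associations of the same standardized size, tested without adjustment.
2. State separately the interaction size detectable at N = 240 and label the moderator analyses exploratory. Until simulated under the study's own model, the approximations above can serve: about 0.35 versus 0 in two equal groups, or a standardized interaction of about 0.18 with a continuous moderator (80% power, two-sided 5%, unadjusted).
3. State the alpha, sidedness and number of tests behind each power figure, and give power at the adjusted level wherever Bonferroni is meant to apply.
4. Correct the 82%, or justify it by describing the simulated model that yields it at r = 0.15 and N = 240.

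The cost is a few sentences and a few more simulation runs, with a more modest power claim for the moderators. Recruitment, data collection and the planned models are unaffected.
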